### **Participants’ experiences of participation**

The experience of participating in the START intervention will be investigated using a qualitative approach where approximately 15 participants from each of the two intervention groups will be interviewed about their experience of participating in the intervention. The interviews will be conducted on one occasion, within 1 month after completion of the intervention. A study-specific interview guide will be used, covering experiences of the intervention in terms of content and its potential benefits or disadvantages. The interviews will be recorded and transcribed verbatim. Qualitative content analysis [64] will be employed. The data collection will take place at a venue of each participant’s choice and it is estimated that it will take 40–60 min.

### Analysis

#### Analysis of quantitative data

Descriptive analysis will be performed and the results will be reported using means ± standard deviations and ranges for continuous variables and numbers and percentages for categorical variables. Data will be analysed with a modified intention-to-treat (ITT) method and all patients involved in at least one data collection will be included in the analysis. Missing values will be imputed with multiple imputation method. Per-protocol (PP) analysis will also be performed where relevant. Analysis of variance (ANOVA) will be performed to compare means of the groups. The differences in baseline characteristics and post-intervention changes between the groups will be tested using *t*-test, Mann-Whitney U test, or Chi-squared test, whichever is appropriate. All analyses will be performed in the statistical software SPSS version 25.0 (IBM Corp., Armonk, NY, US).

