### Sample size estimation

The power calculation is based on the primary outcome, ADHD symptom reduction assessed using the World Health Organization (WHO) Adult ADHD Self-Report Scale (ASRS-v1.1) [32]. Postulating a mean difference in symptom reduction of 15% between the intervention and control groups, with 10.63% SD, 0.05 alpha, 0.8 power and expecting a 25% drop-out, gives a sample size of 120 participants. The actual sample size required for a power of 0.8 is 90 (= 120–120*25%). In case we have larger than 25% drop-out, we will recruit more participants to maintain the necessary power of 0.8.

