### Randomization and blinding

Individuals meeting the inclusion criteria will be randomized into three groups (two intervention groups and one control group) using the Smart-Trial (S-T) electronic data capture platform hosted by Region Örebro County. Randomization will be performed in a 1:1:1 ratio using a block of 6 (9 or 12 to be determined). Stratification will not be applied. During the clinician-rated assessment interview, participants will be instructed not to disclose their group assignment. Due to the nature of the intervention involving structured physical exercise with or without additional person-centred cognitive skills training, blinding of participants to the interventionists in the planned RCT will not be feasible. The individuals collecting the physical tests will also not be blinded to group allocation. However, the data analysts will be blinded to group allocation during the analysis process.

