
### Data collection

Data will be collected before the intervention, during the intervention at week 3, 6 and 9, and directly after the 12-week intervention. Follow-up assessments will be at 6 and 12 months after the start of the intervention. One month after completion of the intervention, a consecutive sample from each of the two intervention groups (n = 15) will be interviewed regarding their experiences of the intervention and eventual benefits.

All online self-assessment scales will be completed digitally in the S-T electronic data capture platform. The data system will automatically send e-mails to participants informing them to log on to the portal to complete the questionnaires, and will notify them when an assessment is approaching or if a questionnaire has not been completed. Notifications will also be sent by e-mail if questionnaires are not completed within the set time frame. Participants who prefer paper questionnaires will have them sent by post together with an envelope with prepaid postage, and questionnaires will be stored in a locked facility at the University Health Care Research Centre at Örebro, to which only the research team will have access. Physical examinations and magnetic resonance imaging (MRI) examinations will be performed during visits to the outpatient clinic and X-ray clinic, respectively.

Data will be collected both in paper and digital formats and stored in locked fireproof cabinets when not being processed, or on a password-protected server within Region Örebro County (RÖL). The material collected will be provided with a code in place of personal data, and only authorized persons will have access to the code key and materials.

Only authorized project members will have access to all folders and subfolders. The principal investigator (MM) and data handlers will have authorization to read and write in the files under project documents, original data, and personal codes. Collected data will be stored in accordance with current legislation and local guidelines for at least 10 years after publication. All project data will be stored on the server, which can only be accessed at RÖL or via a virtual private network (VPN) or, outside RÖL’s area, with a password to the computer and VPN.

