**Primary outcome measures (ADHD symptoms)**								
MADRS-S*	PT					P	P	P
WHO Adult ADHD Self-Report Scale (ASRS-v1.1)		P		P		P	P	P
Clinical Global Impression-Severity (CGI-S)	AP					AP	AP	AP
Clinical Global Impression- Improvement (CGI-I)						AP	AP	AP

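### The named between-group tests are unadjusted for baseline ASRS; adjusting for it would give a more precise primary estimate from data already scheduled

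*Protocol article*

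**What the plan says.** The section Analysis of quantitative data names the tests. It says "Analysis of variance (ANOVA) will be performed to compare means of the groups", and then "The differences in baseline characteristics and post-intervention changes between the groups will be tested using" a t-test, a Mann-Whitney U test or a Chi-squared test, as appropriate. It names no covariate and no repeated-measures model, and does not say whether the means in the ANOVA are post-treatment scores or changes. For missing data it says "Missing values will be imputed with multiple imputation method".

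Table 3 schedules the ASRS at visit 1, 6 weeks, 12 weeks, 6 months and 12 months, so a baseline score is planned for every participant. Allocation is 1:1:1 with 40 per arm, and the section Randomization and blinding adds: "Stratification will not be applied".

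The Sample size estimation section gives the planning inputs: "Postulating a mean difference in symptom reduction of 15% between the intervention and control groups, with 10.63% SD, 0.05 alpha, 0.8 power", with 25% drop-out, 90 evaluable and 120 randomised.

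**The concern.** Baseline severity usually predicts later severity on the same scale. When a baseline score is available, a between-group test that does not estimate this relation leaves explainable variation in the error term. Both named routes do so. A comparison of post-treatment means gives baseline a coefficient of 0, and a comparison of changes gives it a coefficient of 1. The coefficient that minimises the error variance generally lies between the two.

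At stake is the width of the confidence interval for the primary contrast, with about 30 evaluable participants per arm. Validity is not at stake.

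The sentence on changes also plans significance tests of baseline characteristics between randomised groups. Any such difference arises by chance, so those tests do not inform the treatment comparison.

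**Working it through.** **The plan's own figures.** The drop-out step reproduces: 90 / 0.75 = 120. The 90 does not follow from the stated inputs. The standardised effect is 15 / 10.63 = 1.41, and the two-sided two-sample formula gives 2 × (1.96 + 0.84)² × 10.63² / 15² = 7.9, so 8 per arm and 24 over three arms. That is a separate matter. It bears on this point only through power: with 30 per arm the standard error is 10.63 × √(2/30) = 2.74, and power is Φ(15/2.74 − 1.96) = Φ(3.5), above 99.9%. Two-sided testing is assumed, since sidedness is not stated.

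**Variance of the three analyses.** Let baseline X and week-12 score Y each have variance 1 and correlation r (equal variances are assumed). Comparing arms on Y − bX gives a residual variance of 1 − 2br + b².

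- Post-treatment scores (b = 0): 1
- Change scores (b = 1): 2(1 − r)
- Baseline-adjusted (b = r, the minimum): 1 − r²

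The ratio of adjusted to change-score variance is therefore (1 − r²) / [2(1 − r)] = (1 + r)/2. The ratio of adjusted to post-score variance is 1 − r².

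**Results.** The article gives no r, so a range is assumed. The last two columns show how many evaluable participants under adjustment match 90 without it (90 × ratio, rounded up).

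| r (assumed) | Ratio to change | Reduction | Ratio to post | Reduction | N matching 90, change | N matching 90, post |
|---|---|---|---|---|---|---|
| 0.3 | 0.65 | 35% | 0.91 | 9% | 59 | 82 |
| 0.5 | 0.75 | 25% | 0.75 | 25% | 68 | 68 |
| 0.7 | 0.85 | 15% | 0.51 | 49% | 77 | 46 |
| 0.8 | 0.90 | 10% | 0.36 | 64% | 81 | 33 |

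Interval width scales with the square root of the ratio. At r = 0.5 it falls by 13% against either analysis (√0.75 = 0.866). At r = 0.7 it falls by 8% against changes (√0.85 = 0.922) and by 29% against post scores (√0.51 = 0.714).

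**Detectable difference.** With 30 per arm and 80% power, the unadjusted figure is (1.96 + 0.84) × 2.74 = 7.69 percentage points. For r of 0.3, 0.5 and 0.7, adjustment brings it to 6.20, 6.66 and 7.09 if 10.63 is the SD of change, or to 7.34, 6.66 and 5.49 if it is the SD of the post score.

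**What the week-6 ASRS would add at week 12.** With complete data it adds nothing. Suppose 25% are missing at week 12, week 6 is fully observed and all visits are equally correlated. The partial correlation of weeks 6 and 12 given baseline is r/(1 + r). Relative to a complete-case baseline-adjusted analysis, the variance ratio is 1 − 0.25 × [r/(1 + r)]². This is 0.987, 0.972, 0.958 and 0.951 at r = 0.3, 0.5, 0.7 and 0.8, a gain of about 1% to 5%.

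**The case against.** The strongest reply is that a randomised comparison of changes is valid, and that the article is a short summary whose full analysis plan is not shown. Validity stands. The second part does not remove the point: the article names the tests, and both routes it names are unadjusted. This is a stated choice that can be improved, not a missing detail.

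Four stronger readings are tempting, and the documents do not support them.

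- *The analysis ignores baseline.* Change scores subtract it. The sample size section speaks of symptom reduction and the outcome section of changes in symptoms, so changes are the likelier comparator. The smaller gains at higher r (15% at 0.7, 10% at 0.8) therefore deserve more weight than the large ones against post scores.
- *Unstratified randomisation leaves the estimate biased.* Chance imbalance does not bias an unadjusted randomised comparison, and its interval already allows for it. This is the same efficiency point again.
- *The unused repeated ASRS scores cost much precision.* At week 12 they add about 0% to 5%, and the planned multiple imputation could already use them.
- *The trial is underpowered because of this.* On its own inputs it is not.

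A reader might also hold that a Mann-Whitney test cannot be combined with multiple imputation. That is too absolute, because estimates with standard errors can accompany it. Nor is the wording on choosing the appropriate test clearly a data-driven choice for the ASRS, since it covers variables of several types.

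**Conclusion.** The point holds as a recommendation on efficiency. The named tests give an unbiased primary estimate that is less precise than the scheduled data allow. Apart from the one degree of freedom spent on the slope (90 − 3 = 87 residual degrees of freedom become 86), baseline adjustment is at least as precise as either named analysis at any correlation.

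The size rests on an assumed r and on equal variances at the two visits. Over r from 0.3 to 0.7 the variance falls by 35% to 15% against change scores and by 9% to 49% against post scores. Because power on the stated inputs is already very high, the benefit is a narrower interval. It becomes a benefit in power only if the true effect is well below the assumed 1.41 SD.

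**What to change.** Make the primary ASRS analysis at week 12 a linear model with arm as factor and baseline ASRS as covariate. Report MEP against TAU and MEP-C against TAU, each with a 95% confidence interval, in place of the unadjusted ANOVA, t-test or Mann-Whitney test. The model's coefficients and standard errors can be combined over the planned multiple imputations.

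For other scores with a baseline, use the analogous baseline-adjusted analysis at the visits where each is measured. One model form will not serve all of them: Table 3 shows no week-6 CGI-S, for example, and CGI-I has no visit-1 entry to adjust for. Medication use is not a listed measure in Table 3, so it should become a covariate only if its recording is specified.

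A mixed model over the scheduled visits, with baseline ASRS as covariate and arm by visit terms, is an acceptable alternative. It gives one coherent analysis of week 12, 6 months and 12 months but adds little precision at week 12. If it is chosen, state how it sits with multiple imputation and with the control participants whom the Discussion removes from long-term follow-up.

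Drop the significance tests of baseline characteristics and keep the descriptive table. The cost is analysis wording only, since the ASRS scores are already in the schedule. The change should be fixed before the analysts learn the group allocation.

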#### Functional magnetic resonance imaging

A 3.0T MRI system (Signa Premier; GE HealthCare, Waukesha, WI, USA) will be used for structural and fMRI investigations. Data will be preprocessed with slicing-time correction, motion correction, smoothing and registration to a standard template. First-level analysis of the different paradigms (cognitive control, response inhibition and emotion regulation tasks) will be performed using a general linear model (GLM) with task-specific regressors.

#### Analysis of qualitative data

The semi-structured interviews will be analysed using qualitative content analysis. The focus in qualitative content analysis is on variations in the person’s experiences and presenting the results in categories and/or themes [64]. Initially the analysis process will involve getting to know the material, by reading and listening. Thereafter, codes will be generated and categories identified. The coding process will be discussed until agreement is reached between the authors; the codes will then be grouped into subcategories and categories that reflect the core message of the interviews. Thereafter, the subcategories will be abstracted into generic and main categories and the main theme. The data will be analysed using the Qualitative Data Analyses Software (QDAS) in NVivo (QSR International, Inc., Cambridge, MA, USA).

#### Health economic evaluation

A within-trial (3 months) and a long-term (1 year) cost–utility analysis will be performed from both health care and societal perspectives. The base case will consider health care costs and productivity loss. Gained QALYs will be used to measure effects. Cost-effectiveness ratios will be based on changes in QALYs and net costs of the intervention groups versus those in the control group. Results will be presented as an incremental cost-effectiveness ratio (ICER) expressed as (Ca – Cb)/(Ea – Eb). The uncertainty around the cost and effect estimates will be expressed in sensitivity analyses.

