### Aim

The main aim is to implement the 12-week START intervention consisting of a structured MEP with or without cognitive skills training in adults with ADHD, and to study whether it has an effect on core symptoms of ADHD as well as physical, cognitive, mental and everyday functioning, compared with treatment as usual (TAU). TAU consists of pharmacological or non-pharmacological treatment without physical exercise. A further aim is to describe the participants’ experiences of the intervention and its possible benefits, and to evaluate the cost-effectiveness of START compared with TAU.

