**Type of intervention: MEP** – a structured physiotherapy-led exercise programme; or **MEP-C** – MEP together with an occupational therapist-led, person-centered cognitive intervention.**Dose, MEP**: Physical exercise for 45 min, three times a week for 12 weeks. **Dose, MEP-C:** Occupational therapy for 60 min approximately six times (every second week) during the 12-week period depending on participant’s goals related to the intervention; and physical exercise for 45 min, three times a week for 12 weeks.**Dose, MEP**: Physical exercise for 45 min, three times a week for 12 weeks. **Components of physical exercises, MEP and MEP-C**: All exercise sessions will have the same structure and consist of endurance, strength and flexibility training. Desired heart rate (HR) range will be 60–90% of maximum HR. In order to track HR during all sessions, both in the clinic and at home, the participants will have a Polar Heart Rate Monitor, model H10 (Polar Electro Oy, Kempele, Finland), connected to their mobile phone. Each exercise session will start with 5–10 minutes’ **warm-up** on an ergometer or using body movements. Next will be **endurance exercises** in three to five intervals of 1 min work and 1 min active rest between each interval. The **strength training exercises** will consist of five different exercises with 1-minute intervals between exercises, in three rounds. These strength exercises may vary depending on the location, indoors or outdoors. However, they will always include one exercise mainly for leg strength, for example squats or lunges; one exercise for arms and shoulders, for example shoulder press with barbell or bench press; one core exercise, for example crunches or the plank; and one balance challenge, for example standing on one leg. The participants will be encouraged to do as many repetitions as possible in 1 min and therefore the load of the exercise can be altered depending on the number of repetitions the participant can manage. In the cool-down, in the warm-up and during stretching the participant will be encouraged to sense the feeling of the body and their overall feeling.**Components of the cognitive intervention of the MEP-C**: As previously mentioned, the cognitive intervention will be conducted by an occupational therapist on approximately six occasions during the 12-week period. Based on self-prioritized goals concerning structure, planning and organization in everyday life, a treatment plan for cognitive skills training will be drawn up. This will form the basis of the treatment. (Examples of such goals are: to arrive on time for training, or to create the space for physical activity in one’s everyday life through improved time management.)**Sequences**: The training sessions will take place either in the training facilities at the outpatient clinic or outdoors in a nearby park. Each session will follow a specific structure.**Modifications**: Alternative exercises will be suggested by the instructors when needed. Participants will be allowed to perform to the best of their ability, with encouragement from the physiotherapists to use maximum effort.**Selection of instructors**: The instructors for the physical exercise sessions will be licensed physiotherapists at the Unit for Psychiatric Physiotherapy, Region Örebro County, who are experienced in working with persons with ADHD. The instructors for the cognitive intervention will be occupational therapists with experience of both working with persons with ADHD and using the Canadian Occupational Performance Measure (COPM) as person-centred tool [33, 34].**Home practice**: In addition to the physiotherapist-led group, the participants will be expected to exercise individually once a week, to the extent needed to reach 150 minutes’ exercise per week. Participants receiving cognitive skills training will be given home assignments, primarily to implement compensatory cognitive strategies in daily life.**Fidelity**: Training adherence will be noted by the treating physiotherapist and occupational therapist. Group adherence to physical activity will be calculated as the number of patients attending 50% of the sessions. To maintain physical exercise for at least 150 min per week, the HR monitor connected to the participants’ mobile phone will gather the time in an HR zone of > 60%. Attendance rate over the intervention period will be calculated as a mean of the individual percentage.**Control group**: Participants randomized to the control group will continue with their TAU. This will include any ongoing pharmacological and/or non-pharmacological treatment that does not include physical exercise or cognitive skills training during the 12-week period. After the 12-week data collection, the participants will be offered physiotherapy-supported training outside the framework of the study.

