### Secondary outcome measures

Clinical variables:

The Patient-rated Global Impression-Improvement scale (PGI-I) [35].The EQ-5D-5 L [37, 38], developed by the EuroQol Group. The EQ-5D-5 L is a QoL measure for assessing an individual’s health status, using a 5-level scale ranging from “no problem” to “extreme problems”, divided into five dimensions of mobility, self-care, usual activities, pain/discomfort, and anxiety/depression. The EQ-5D-5 L can also be used to generate a utility value that ranges from 0 (dead) to 1 (perfect health). By multiplying the time spent in a given health state (baseline – 3 weeks – 6 weeks – 9 weeks – 6 months – 12 months) by the average utility weight associated with the period (using the trapezium rule), quality-adjusted life years (QALYs) will be derived. This will be used in the health economic evaluation.

Physical function:

The Ekblom-Bak (EB) submaximal exercise test. The EB test is a valid measure of maximal oxygen uptake (VO_2_max) for a wide variety of ages [39, 40].The Flamingo balance test is a 60-second one-leg stand test measuring static balance and stability in the abdominal, pelvic and leg muscles [41, 42].Grip strength measured with a hand-held dynamometer JAMAR, (Item 3363, G.E. Miller, Inc., [name]) a reliable and valid measure in healthy participants as well as across various clinical populations [43, 44], will be tested, and height, weight and waist circumference will be measured using standardized tests [45]. Thereafter, body mass index (BMI) will be calculated.The Body Awareness Scale-Movement Quality and Experience (BAS MQ-E) will be used for physiotherapeutic assessment of body awareness [46]. The psychometric properties of this scale have been reported to be good [47].An accelerometer (Actigraph GT3X+; ActiGraph, Pensacola, FL, USA) will be used to measure levels of daily physical activity and general health [48–51].The Swedish National Board of Health and Welfare’s indicator questions about exercise and training habits [52] will be used to assess physical function.

Cognitive function:

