
Cost estimates for the health economic evaluation:

Health care consumption and productivity loss (sick leave) will be estimated using data from administrative systems and/or medical records in health care. Costs will be estimated by multiplying frequencies by national Swedish tariffs and market prices. Total costs for each group will be aggregated over the trial period.Intervention cost will be estimated based on information provided by the persons responsible for the intervention.

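### The planned cost-effectiveness ratios compare the active arms only with TAU, so the plan does not yield the incremental ratio of MEP-C over MEP

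*Protocol article*

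**What the plan says.** The Aim section sets the economic question as "to evaluate the cost-effectiveness of START compared with TAU", and the abstract's objective does the same. The Health economic evaluation section carries this into the method: "Cost-effectiveness ratios will be based on changes in QALYs and net costs of the intervention groups versus those in the control group". It continues: "Results will be presented as an incremental cost-effectiveness ratio (ICER) expressed as (Ca – Cb)/(Ea – Eb"), without saying which arms a and b stand for. It also does not say whether the two active arms are each compared with TAU or pooled. Two horizons are planned: "A within-trial (3 months) and a long-term (1 year) cost–utility analysis will be performed from both health care and societal perspectives".

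No section mentions a ratio of MEP-C against MEP, an ordering of the three arms by cost, or a rule for dominated options. The resource difference between the active arms is described in the intervention section. MEP-C adds "Occupational therapy for 60 min approximately six times (every second week) during the 12-week period" to the same exercise programme.

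On the ingredients, the Secondary outcome measures section gives the utility side as "average utility weight associated with the period (using the trapezium rule), quality-adjusted life years (QALYs) will be derived" and the cost side as "Total costs for each group will be aggregated over the trial period". On uncertainty, the plan says only: "The uncertainty around the cost and effect estimates will be expressed in sensitivity analyses".

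**The concern.** A service deciding what to offer has three mutually exclusive choices. With more than two options, the informative ratio for the more intensive one is against the next less costly option that is not dominated. Here that is most likely MEP-C against MEP, because MEP-C is the same exercise plus therapist time.

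The ratio of MEP-C against TAU mixes two things: what exercise buys, and what the occupational therapy sessions buy on top. If exercise is good value, it can carry a poor-value addition under an acceptable overall ratio. The plan as written yields no output that would reveal this. The trial was designed to study exercise with and without cognitive skills training, so a reader will naturally ask what the addition is worth.

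**Working it through.** The plan states no ICER, cost, utility, utility SD or willingness-to-pay threshold, so there is no figure to reproduce. The check is whether ratios against TAU alone can mislead, using the plan's own formula with assumed inputs. Costs are in arbitrary units, and TAU is the zero point.

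**1. Extra resource in MEP-C** (intervention section): about 6 × 60 min = about 6 hours of occupational therapy per participant.

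**2. First illustration (assumed):** MEP +500 and +0.020 QALY; MEP-C +1,100 and +0.025 QALY.
- MEP vs TAU: 500 / 0.020 = 25,000
- MEP-C vs TAU: 1,100 / 0.025 = 44,000
- MEP-C vs MEP: (1,100 − 500) / (0.025 − 0.020) = 600 / 0.005 = 120,000

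At any threshold between 44,000 and 120,000, MEP-C passes against TAU and fails against MEP.

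**3. If the active arms were pooled** (equal size, same inputs): mean cost (500 + 1,100) / 2 = 800; mean gain (0.020 + 0.025) / 2 = 0.0225; ratio 800 / 0.0225 = 35,556. This hides the addition altogether.

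**4. Ratios alone do not let a reader recover the missing one.** Suppose MEP-C were +2,200 and +0.050 QALY. Its ratio to TAU is again 2,200 / 0.050 = 44,000, but against MEP it is (2,200 − 500) / (0.050 − 0.020) = 56,667, not 120,000.

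**5. Second set of assumed inputs, to see how general this is.** MEP-C costs +16,000 and MEP +8,000 throughout.

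| MEP QALY gain | MEP-C QALY gain | MEP vs TAU | MEP-C vs TAU | MEP-C vs MEP |
|---|---|---|---|---|
| 0.030 | 0.035 | 266,667 | 457,143 | 1,600,000 |
| 0.030 | 0.040 | 266,667 | 400,000 | 800,000 |
| 0.030 | 0.060 | 266,667 | 266,667 | 266,667 |
| 0.020 | 0.045 | 400,000 | 355,556 | 320,000 |

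The first two rows mislead at an assumed threshold of 500,000; the last two do not. With MEP at +0.030 and that threshold, MEP-C passes against TAU once its gain reaches 16,000 / 500,000 = 0.032. It passes against MEP only once its gain reaches 0.030 + 8,000 / 500,000 = 0.046. Between 0.032 and 0.046 the two answers disagree. The gain over MEP needed to justify an extra 8,000 is 0.027 QALY at a threshold of 300,000, 0.016 at 500,000 and 0.008 at 1,000,000.

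**6. Side check on baseline utility.** QALYs by the trapezium rule include the baseline value. With an assumed utility SD of 0.15 to 0.25 and 40 per arm, the SE of a between-arm baseline difference is SD × √(2/40) = 0.034 to 0.056. Carried forward in full, one SE is 0.034 to 0.056 QALY at 1 year, and × 12/52 = 0.008 to 0.013 QALY at 12 weeks. This would matter only if the analysis were unadjusted, which the article does not say.

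**The case against.** The strongest defence is that the plan answers the question it sets. The aim is START against usual treatment, and a ratio against TAU is a correct answer to that. Harm arises only if someone uses it to choose between MEP and MEP-C, a conclusion the article does not say it will draw. This stands, and it limits the point: the plan is incomplete for a three-option decision, not wrong for its stated aim.

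It can also be said that costs are totalled by group and utilities are collected, so the missing comparison could be obtained by subtraction. That holds for the point estimate if incremental costs and QALYs are published separately for each active arm. It fails if only ratios are given or the arms are pooled (steps 3 and 4). It also gives no interval, because the two contrasts share the TAU arm.

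A reader might infer more than the text supports:
- **That QALYs will not be adjusted for baseline utility.** Adjustment is neither stated nor excluded. A condensed article commonly leaves this to an analysis plan, and none is shown.
- **That sampling uncertainty will be ignored.** The kind of sensitivity analysis is not specified and could be probabilistic. This calls for clarification and is not an error.
- **That chance baseline imbalance could match the QALY gain sought.** The documents state no such gain.
- **That the conclusion on MEP-C will be wrong in direction.** The last two rows of the table show inputs for which it would not be.

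Neither baseline adjustment nor the handling of uncertainty produces the gap between the TAU and MEP comparisons. Only the choice of comparator does.

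**Conclusion.** The point holds on the comparator. The stated ratios are against control only, and the formula's terms are undefined. The plan therefore does not produce the MEP-C versus MEP ratio needed to choose among three mutually exclusive options. An acceptable ratio against TAU can coexist with one against MEP that is about two to three and a half times as large on the assumed inputs (800,000 / 400,000 = 2.0; 120,000 / 44,000 = 2.7; 1,600,000 / 457,143 = 3.5). On other inputs the gap vanishes or reverses. All of these figures rest on assumed costs, QALY gains and thresholds; what the documents establish is only the missing comparison. Cost-effectiveness is a secondary aim, so the trial's primary conclusion is not affected.

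**What to change.** In the Health economic evaluation section:
1. State that MEP and MEP-C are analysed as separate arms, and say what a and b denote.
2. Order the three arms by mean cost, remove dominated options, and report sequential ICERs or net benefit, including MEP-C versus MEP, at 3 months and 1 year. Keep the planned comparisons with TAU alongside.
3. As an inexpensive improvement, estimate QALY differences by regression on arm and baseline EQ-5D utility, which is already collected.
4. Say what kind of sensitivity analysis will express uncertainty. Bootstrapping participants' costs and QALYs jointly would give intervals for net benefit.

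The cost is a few sentences and some additional programming, with no new data. The MEP-C versus MEP estimate will be imprecise at 40 per arm and should be presented with its interval. The Discussion removes from long-term follow-up any control participants who start the physiotherapy-led intervention. That complicates the 1-year comparisons with TAU, but the rule concerns controls only and does not bear on MEP-C versus MEP.
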